# A randomized interventional parallel study to evaluate the effect of pelvic floor muscle training with stabilization exercises of high and low intensity in women with stress urinary incontinence

**DOI:** 10.1097/MD.0000000000021264

**Published:** 2020-07-17

**Keywords:** 2D/3D ultrasound, high-/low-intensity, pelvic floor exercise, stress urinary incontinence

## Abstract

**Introduction::**

The effect of different intensities of pelvic floor muscle training (PFMT) assessed by 2D/3D ultrasound (USG) have not been sufficiently monitored in the literature. The objective of the study will be to evaluate the effect of this intervention by assessing the change in incontinence episode frequency, hiatal area (HA) and hiatal diameter by 2D/3D USG and quality of life over 12 weeks of treatment.

**Methods::**

Using a randomized interventional parallel study, patients will be assigned to groups A and B using simple software randomization according to odd and even patient sequence numbers. The following methods will be used for evaluation: change in incontinence episode frequency, power and endurance of pelvic floor muscles assessed by perineometer (in cmH_2_O), HA (in cm^2^) during contraction, Valsalva manoeuvre assessed by 3D USG, hiatal diameter assessed by 2D USG, the Incontinence Quality of Life scale (I-QoL) and the Patient Global Impression of Improvement score (PGI-I). Interventions: Group A, high-intensity PFMT 5 times a week for 30 minutes per day. Group B, low-intensity PFMT twice a week for 15 minutes per day. The duration of the intervention will be 12 weeks.

**Discussion::**

The study protocol presents the starting points, design, and methods of the PELSTAB Study. We expect that, after 12 weeks of high-intensity PFMT, women with stress urinary incontinence will have significantly less incontinence episode frequency, better reduction of HA during contraction and Valsalva manoeuvre, higher power and endurance of pelvic floor muscles and better quality of life compared to the group with low-intensity PFMT.

**Registration::**

This study was registered in the ClinicalTrials.govNCT04340323.

## Introduction

1

Stress urinary incontinence (SUI), defined as “complaint of involuntary loss of urine on effort or physical exertion (e.g., sporting activities) or on sneezing or coughing.” Missing are the symptoms of an overactive bladder—urgency, nocturia, and enuresis.^[1,4]^ Irrespective of age, 15% to 30% of women are affected by urinary incontinence in all areas of their lives—physical, mental and social—with subsequent deterioration in quality of life.^[2]^

The method of first choice in the treatment of SUI, according to the International Continence Society (ICS), is pelvic floor muscle training (PFMT). PFMT is a method based on scientific evidence, defined by the ICS as repeated selective voluntary contraction and relaxation of specific pelvic floor (PF) muscles. It is important not only to train the strength and endurance of the PF muscles but also their relaxation.^[1–4]^ Some authors have applied PFMT in combination with stabilization exercises for the management of SUI.^[5]^ Many women do not adhere to the frequency and intensity of exercise, according to the recommendations of physiotherapists. They practice PFMT less often and for shorter periods. The effect of different intensities of PFMT on SUI has not been sufficiently monitored in the literature.

Globally, there are not enough published studies with the objectivization of PFMT by means of 3D ultrasound examination of PF muscles.^[6,7]^ In gynecology and urology, 2D/3D ultrasound (USG) is a standard examination. However, it is also important to objectify the results of physiotherapy treatment this way. Some studies have been conducted in which 2D USG was used for measures of PF function (e.g., change in levator plate angle and reductions in hiatal diameter and bladder neck displacement.^[8,9]^ However, these examinations do not show the hiatal space and musculus levator ani. Thus, monitoring the PF muscle complex at rest, in contraction and during the Valsalva manoeuvre (VM), as well as measuring muscle volume and thickness and visualizing muscle damage, is inadequate with 2D imaging. Our study would be the first to monitor the hiatal space and musculus levator ani after 12 weeks of PFMT with high- and low-intensity using 3D USG imaging.

### Primary goal

1.1

The primary objective of this study will be to evaluate the effect of high- and low-intensity PFMT with stabilization exercises in women with SUI by assessing the change in incontinence episode frequency (IEF) over 12 weeks of treatment.

### Secondary goal

1.2

The secondary objective of this study will be to evaluate the effect of high- and low-intensity PFMT with stabilization exercises in women with SUI by assessing change in power and endurance of PF muscles assessed by perineometer, change in hiatal area (HA) during contraction and the VM assessed by 3D USG, hiatal diameter assessed by 2D USG, change of QOL assessed by the incontinence quality of life scale (I-QoL) and assessment of the patient global impression of improvement score (PGI-I) over 12 weeks of treatment.

## Methods

2

### Study design

2.1

This randomized interventional parallel study is a controlled study that compares the effect of different intensities of PFMT with stabilization exercises in women with SUI. The objectification of power and endurance of PF muscles will be made using perineometry and imaging of HA during contraction and the VM will be made using 2D/3D USG. The hypothesis is that, after 12 weeks of high-intensity PFMT, women with SUI will have significantly fewer IEF, better reduction of HA during contraction and VM, higher power and endurance of PF muscles and better QOL compared to the group with low-intensity PFMT. The protocol was approved by the Ethics Committee of the Košice self-governing region (no. 3545/2020/ODDZ-06621). Informed consent will be obtained from trial participants by the local gynecology clinic. The personal information about potential and enrolled participants will be collected, shared, and protected in concordance with Slovakian law.

### Recruitment and consent

2.2

All potential participants from regional gynecological outpatient clinics will be selected by a gynecologist based on inclusion and exclusion criteria and will receive written information about the study. They will then sign an informed consent form. Gynecologists, based on inclusion and exclusion criteria, will confirm patient inclusion and provide study details. Data will be collected and patients will be treated at the Outpatient Clinic Centrum S.R.O. in Košice, Slovakia. The study will be conducted in 2 parallel groups: Group A, high-intensity exercise group, 5 times a week for 30 minutes per day; Group B, low-intensity exercise group, twice a week for 15 minutes per day. This is a randomized controlled study with a 1:1 ratio. For the allocation process, computer-generated sequences will be used, and the researcher will not participate in the study. The computer generates even and odd patient numbers: odd patient numbers, high-intensity exercise; even patient numbers, low-intensity exercise. The generated numbers will be placed in sealed envelopes, and each envelope will contain the group code. Blinding will prevent intentional selection (Table 1).

**Table 1 T1:**
[figure not shown]
Recruitment, intervention and evaluation plan for groups in the PELSTAB study.

Details of study are described in primary and secondary measurements, adverse events and interventions sections.

### Sample size

2.3

We used an estimate according to selection of the sample of probands based on the test strength of 0.80 and alpha = 0.05 (type I error). The number of probands in the Group A and Group B will be 34 in each, giving a total of 68. We expect a 20% loss, so we will include 86 probands. Based on sample selection, we expect a decrease in incidence after intervention from 25% to 10%. We will consider the treatment to be successful if there is a decrease of more than 50%.

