### Inclusion criteria

2.4

1.Women willing to provide written informed consent.2.Women over 18 years old who experience uncomplicated SUI.3.Score on the International Consultation on Urinary Incontinence Questionnaire of ≥6 points4.Symptoms of urinary incontinence for at least 3 consecutive months.5.Degree of pelvic organ prolapse, stage ≤2.6.Willingness to accept the randomization process and fully participate in tests.

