##### Change in IEF over 1 week

2.7.1.1

Urine leakage symptoms were reported according to an assessment of the number of incontinence episodes per week (or IEF).

SUI is confirmed with a positive score on the ICIQ-UI and a negative symptom score on the overactive bladder questionnaire (OAB-q). Both overactive bladder and urge urinary incontinence were excluded by the OAB-q.

The International consultation on urinary incontinence questionnaire short form (ICIQ-UI SF) was developed by the ICS. The first 2 questions on the ICIQ-UI monitor the frequency and quantity of leaked urine, and the third question considers how urine loss affects the daily lives of women. The ICIQ-UI score is the sum of all questions (0 = no leak; 1–5 = slight; 6–12 = moderate; 13–18 = severe; 19–21 = very serious). Cronbach alpha reliability is 0.95.^[10,11]^

The OAB-q focuses on the symptoms of an overactive bladder over the last 4 weeks. It contains 6 questions on symptoms, giving the symptom score (0, without symptoms; 100, most symptoms), and 13 questions that assess QOL (100, best QOL; 0, worst QOL). Cronbach alpha is 0.90.^[12,13]^

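### The stated 80% power with 34 women per group is not supported by the only effect assumption given (25% to 10%), which is not on the primary endpoint

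*Protocol article*

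**What the plan says.** Section 2.3 (Sample size) sets power at 0.80 and alpha at 0.05, without saying whether the test is one- or two-sided. It then gives the size: "The number of probands in the Group A and Group B will be 34 in each, giving a total of 68". Attrition follows: "We expect a 20% loss, so we will include 86 probands". The one effect assumption comes after these figures: "we expect a decrease in incidence after intervention from 25% to 10" per cent. The section does not say what the incidence is of, or to which arm or time point each rate belongs. It closes by calling treatment successful if the decrease exceeds 50%. The Discussion ties that rule to weekly IEF, but no expected success rate is given for either arm.

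Elsewhere, section 1.1 defines the primary objective through "assessing the change in incontinence episode frequency (IEF) over 12 weeks of treatment", and section 2.7.1.1 defines IEF as a number of episodes per week. Section 2.1 hypothesises that high intensity does better than low intensity. Section 2.9 plans a mixed-design repeated-measures ANOVA. Section 2.4 requires stress urinary incontinence, an ICIQ score of at least 6, and "Symptoms of urinary incontinence for at least 3 consecutive months".

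**The concern.** A sample size statement should allow a reader to get from the assumed effect to the number of patients. Here two things stand in the way.

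First, the assumption concerns a different quantity from the one the trial tests. It is a pair of percentages, whereas the endpoint is a count per week analysed by ANOVA. It is worded as a fall over time, whereas the hypothesis compares two arms, and no low-intensity result is assumed. If the incidence is that of incontinence, 25% cannot be the starting value in women who are all incontinent.

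Second, taking the two percentages at face value, 34 per group looks far too few.

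At stake is the claim of 80% power itself. Readers will use it to judge how much a non-significant comparison of the two intensities tells them.

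**Working it through.** **Inputs from the article.** Power 0.80, alpha 0.05, 34 per group, 20% loss and 86 enrolled (section 2.3); 1:1 allocation (section 2.2); rates 0.25 and 0.10 (section 2.3). **Assumption:** two-sided testing, with one-sided shown as well. Normal quantiles: 1.960 (two-sided), 1.645 (one-sided), 0.842 (80% power).

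**1. The loss step reproduces.** 34/0.8 = 42.5, rounded up to 43 per group, and 2 × 43 = 86. The enrolment figure is not at issue.

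**2. Rates read as a difference between groups.** The mean rate is 0.175.
- Formula: n = [z_α √(2·0.175·0.825) + z_β √(0.25·0.75 + 0.10·0.90)]² / 0.15².
- Two-sided: (1.960 × 0.5374 + 0.842 × 0.5268)² / 0.0225 = 99.5, so 100 per group.
- Unpooled variance: 0.2775 × (1.960 + 0.842)² / 0.0225 = 96.8, so 97. The arcsine method also gives 97. With continuity correction, 113.
- One-sided, pooled: 78.3, so 79.
- Power at 34 per group: Φ[(0.15 × √34 − 1.960 × 0.5374) / 0.5268] = Φ(−0.339) = 36.7%. By other methods: 38.1% (exact chi-square), 26.2% (Fisher), 49.3% (one-sided, pooled).
- Power at 43 per group (all 86 retained): 44.7% two-sided.

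**3. Rates read as before-after.**
- Paired (McNemar), most favourable case with no woman worsening: [1.960 √0.15 + 0.842 √(0.15 − 0.0225)]² / 0.0225 = 49.9, so 50 women two-sided; one-sided, 39.1, so 40. Power with 34 women is 62.7% two-sided and 74.7% one-sided.
- One-sample test against a fixed 25%: [1.960 √(0.25·0.75) + 0.842 √(0.10·0.90)]² / 0.0225 = 53.9, so 54 two-sided; one-sided, 41.4, so 42. The arcsine version gives 49 and 38.
- If both arms are pooled, 68 women can reach 80%: the most favourable McNemar case has 91.0% power two-sided. But a pooled before-after test says nothing about high against low intensity.

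**4. What 34 per group does support.** For a two-sample comparison of means, the detectable difference is (1.960 + 0.842) × √(2/34) = 0.68 SD by normal approximation, or 0.69 SD by t test. Conversely, a t test for a difference of 0.70 SD needs 33.02 per group, which rounds up to 34.

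**5. Effect of the pre-post correlation r (assumed; the article gives none).** Take equal SDs at both times and express the difference in SDs of IEF itself. An analysis of change detects 0.69 × √(2(1 − r)); a baseline-adjusted analysis detects 0.69 × √(1 − r²).

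| r | change | baseline-adjusted |
|---|---|---|
| 0.3 | 0.82 | 0.66 |
| 0.5 | 0.69 | 0.60 |
| 0.7 | 0.53 | 0.49 |

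**The case against.** The best defence is that section 2.3 never says 34 was calculated from 25% and 10%. The sentence comes after the numbers and is phrased as an expectation. A round standardised difference of 0.7 gives exactly 34, so the authors may have used it and left it out of a condensed article. This is plausible and it stands: a reader might infer that the authors made an arithmetic slip, and the article does not show that. Nor does it state 0.7, however, so the possibility does not repair the text.

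A second defence is that the rates describe a change over time, so treating 25% as the low-intensity rate and 10% as the high-intensity rate is the reviewer's construction. This also stands. A reader might infer that the trial has 37% power, or would miss its effect about two times in three. The article does not support that, because the planned test is an ANOVA on IEF and no IEF difference or SD is given.

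Third, some less usual variants come near the stated numbers. A one-sample formula using only the 10% variance gives 32. One using only the 25% variance gives 66, against the total of 68. A two-sided McNemar test on all women, assuming 17.5% improve and 2.5% worsen, gives 68. None is described in the article and none compares the arms.

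Finally, a reader might fear that a null result will be taken as equivalence. The article plans no such conclusion, so that is a risk of interpretation and not an error in the plan.

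**Conclusion.** The point holds. The 80% power claim for the comparison of high with low intensity is unsupported by the one effect assumption printed beside it. That assumption is off the primary endpoint, does not fit the enrolled population if it means incontinence, and is not assigned to arms. Whichever formula was used, it cannot justify the size of this trial.

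The mismatch is large. On a between-group reading the assumption needs about three times the stated number per group (97 to 113 against 34). On a before-after reading within a group, the usual calculations need about 50 to 54 two-sided, or 40 to 42 one-sided; the arcsine approximation lowers these only to 49 and 38.

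The 37% (two-sided) and 49% (one-sided) figures hold only if the rates are taken as the two arms' results, so they are not estimates of the trial's power. That power for IEF cannot be calculated from the article. What can be said is that 34 per group would suit a standardised difference of about 0.7, which is not stated.

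**What to change.** Keep the enrolment target of 86. Delete the 25% to 10% sentence; keeping it with a power of 37% attached would retain an assumption that does not describe the endpoint or the comparison. Replace it with wording such as: with 34 evaluable women per group, the trial has 80% power at two-sided alpha 0.05 to detect a between-group difference of about 0.69 SD in change in weekly IEF, which is X episodes per week for an SD of Y. X and Y should come from a source that the authors name. If a gain from baseline adjustment is claimed, show it over a range of assumed pre-post correlations, as in the table above, and not at one favourable value.

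The cost is a rewritten paragraph and a less favourable stated figure, since about 0.7 SD is a sizeable difference to expect between two intensities of the same training. No extra patients are required.

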### Inclusion criteria

2.4

1.Women willing to provide written informed consent.2.Women over 18 years old who experience uncomplicated SUI.3.Score on the International Consultation on Urinary Incontinence Questionnaire of ≥6 points4.Symptoms of urinary incontinence for at least 3 consecutive months.5.Degree of pelvic organ prolapse, stage ≤2.6.Willingness to accept the randomization process and fully participate in tests.

### Exclusion criteria

2.5

1.History of anti-incontinence surgery in the past 12 months.2.History of pelvic prolapse repair or urethral surgery in the past 12 months.3.History of PFMT in the past 12 months.4.History of interstitial cystitis or bladder-related pain.5.Chronic severe constipation.6.Clinically significant renal or hepatic impairment.7.Clinically significant heart impairment.8.Pregnant, lactating or actively trying to become pregnant.9.Positive urinary tract infection.10.Use of rehabilitation aids (pessary, urethral plugs, vaginal beads, etc.).11.Insufficient understanding of PF exercises and/or omitting exercises.12.Incomplete questionnaire.13.Refusal to participate in the study.

### Interventions

2.6

The duration of PFMT with lumbopelvic stabilization will be 12 weeks (Table 2).

**Table 2 T2:**
[figure not shown]
Exercise protocol.

#### Both groups

2.6.1

1.Educating probands about anatomy, physiology, and PF muscle function.2.Training of PF muscles in different positions (lying on back, on abdomen, sitting, standing, and walking).3.Training of PF muscles with activation of deep trunk muscles, or stabilization exercises (Table 2).

Exercise performance and strength and endurance training during the following exercises:

Diaphragmatic breathing and activation of musculus transversus abdominisStabilization during bridgeDiagonal stabilizationStabilization in the push-upStabilization during squatsStabilization during side bridge.

#### Group A (high-intensity exercise group)

2.6.2

Dosage of exercise: 12 weeks, 5 times a week for 30 minutes per day, with 5 educational sessions by a physiotherapist, followed by continuation at home.

#### Group B (low-intensity exercise group)

2.6.3

Dosage of exercise: 12 weeks, twice a week for 15 minutes per day, with 5 educational sessions by a physiotherapist, followed by continuation at home.

### Outcome measures

2.7

Outcome measures before treatment and over 12 weeks of treatment.

#### Primary measurements

2.7.1

##### Change in IEF over 1 week

2.7.1.1

Urine leakage symptoms were reported according to an assessment of the number of incontinence episodes per week (or IEF).

SUI is confirmed with a positive score on the ICIQ-UI and a negative symptom score on the overactive bladder questionnaire (OAB-q). Both overactive bladder and urge urinary incontinence were excluded by the OAB-q.

The International consultation on urinary incontinence questionnaire short form (ICIQ-UI SF) was developed by the ICS. The first 2 questions on the ICIQ-UI monitor the frequency and quantity of leaked urine, and the third question considers how urine loss affects the daily lives of women. The ICIQ-UI score is the sum of all questions (0 = no leak; 1–5 = slight; 6–12 = moderate; 13–18 = severe; 19–21 = very serious). Cronbach alpha reliability is 0.95.^[10,11]^

The OAB-q focuses on the symptoms of an overactive bladder over the last 4 weeks. It contains 6 questions on symptoms, giving the symptom score (0, without symptoms; 100, most symptoms), and 13 questions that assess QOL (100, best QOL; 0, worst QOL). Cronbach alpha is 0.90.^[12,13]^

#### Secondary measurements

2.7.2

##### Change in performance and endurance of PF muscles

2.7.2.1

1A. The PERFECT scheme^[14]^ provides information on the functional state of the PF muscles and monitors several important parameters:

P – Power. A 5-point scale is used (no contraction, weak contraction, normal contraction, strong contraction, and very strong contraction).

E – Endurance. The patient is requested to perform a maximum voluntary contraction (MVC) of the PF, and the contraction weakening time is measured. The time is given in seconds, for a maximum of 10 seconds.

R – Repetitions. The patient is requested to perform repeated MVCs for 3 seconds. The number of contractions to fatigue or a decrease in quality (up to 10 contractions) is recorded.

F – Fast contractions. The patient is requested to perform rapidly repeated MVCs lasting a maximum of 1 second each. The number of contractions to fatigue or quality decline (up to 10 contractions) is recorded.

E, C, T – Every Contraction Timed. A reminder to time every contraction.

1B. Relaxation of the PF muscles

The ability of the PF muscles to relax after a MVC: absent = 2, partial = 1 and complete = 0.^[15]^

1C. PF examination by perineometer (Peritron-Ontario L4V, Canada)

Perineometric pressure during a MVC, endurance, and PF muscle relaxation in units of water column height (cmH_2_O) were objectivized. A pressure probe up to 11 cm was used, with a latex condom to which a lubricant was applied. Examination was carried out with an empty bladder in the lithotomy position. The probe was inserted vaginally without pain or discomfort. Three MVCs were performed over a period of 4 seconds. Up to 10 mmHg is a slight contraction, 10 to 30 cmH_2_O is a moderate contraction and 40 to 60 cmH_2_O is a strong contraction. It is important to set the resting tone correctly after saturation introduction to 100 cmH_2_O.^[16]^

1D. PF muscle resting tone

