### Data analysis

2.9

Descriptive and analytical statistics will be used for data analysis. An unpaired *t* test will be used to compare the experimental and control groups before training. Differences between the control and experimental groups at pre- and post-intervention will be assessed using a generalized linear model repeated-measures mixed-design ANOVA (significance level, *P* < .05), and partial eta-squared (η^2^) effect sizes will be calculated. According to Cohen's (1988) specification for ANOVA analysis, effect sizes were classified as follows: η^2^ = 0.00–0.003, no effect size; η^2^ = 0.010–0.039, small effect size; η^2^ = 0.060–0.110, medium effect size; and η^2^ = 0.140–0.200: large effect size. Calculations will be evaluated in IBM SPSS 25 Windows (IBM, Chicago, IL).

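### Three PERFECT items stop at 10 s or 10 contractions; comparing mean change as if 10 were exact would pull the arm difference toward zero if many women reach the cap

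*Protocol article*

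**What the plan says.** Section 2.7.2.1 of the protocol article lists the PERFECT scheme (1A) first among the secondary measurements of pelvic floor performance and endurance. Three of its items have an upper limit:

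- Endurance, the time until a maximal contraction weakens: "The time is given in seconds, for a maximum of 10 seconds".
- Repetitions: "The number of contractions to fatigue or a decrease in quality (up to 10 contractions) is recorded".
- Fast contractions: "The number of contractions to fatigue or quality decline (up to 10 contractions) is recorded".

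Section 2.9 names one method for the pre/post comparison. Differences between the groups "will be assessed using a generalized linear model repeated-measures mixed-design ANOVA". It does not say which outcomes this covers and gives no other method for bounded scores. Section 2.1 expects the high-intensity arm to show "higher power and endurance of PF muscles and better QOL compared to the group with low-intensity PFMT".

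Two other places limit what follows. The secondary goal (section 1.2) is "change in power and endurance of PF muscles assessed by perineometer", so the declared instrument is the perineometer. Item 1C of section 2.7.2.1 records "Perineometric pressure during a MVC, endurance, and PF muscle relaxation in units of water column height", and no cap is stated for it.

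**The concern.** A woman who could hold for 14 s is recorded as 10, the same as a woman who weakens at exactly 10 s. A recorded 10 therefore means 10 or more; the value is right-censored. With two arms and two visits, the group-by-time test of the mixed ANOVA is the test of the difference in mean change, and it takes 10 at face value. A woman already at the cap at baseline cannot show a gain, and one who passes it by week 12 has her gain cut short.

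Randomised arms have equal baselines in expectation. If the high-intensity arm truly gains more, as the hypothesis predicts, the cap removes more from that arm. A small or null PERFECT result could then reflect the cap and not the training. No eligibility criterion sets a level of pelvic floor function, so women near the cap at baseline can enter.

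**Working it through.** The article gives no PERFECT baseline, SD, expected gain or power, so there is no stated figure to reproduce.

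**Inputs.** From the article: the cap of 10 s, two arms, two time points, 34 per arm (section 2.3). Assumed: normal values, SD 3 s at each visit, pre-post correlation 0.5, true difference 2 s, equal baselines.

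**1. Expected capped difference.** Equal baselines cancel, so the expected difference in mean change equals the difference in capped week-12 means. For a normal variable with mean μ and SD σ, with z = (10 − μ)/σ:

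E[min(Y, 10)] = μΦ(z) + 10(1 − Φ(z)) − σφ(z), and the share at the cap is 1 − Φ(z).

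At 10 v 8 s:
- μ = 10, z = 0: 10 × 0.500 + 10 × 0.500 − 3 × 0.399 = 8.80
- μ = 8, z = 0.667: 8 × 0.7475 + 10 × 0.2525 − 3 × 0.3194 = 7.55
- Difference 1.26 s from unrounded values; loss (2 − 1.26)/2 = 37%.

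At 6 v 4 s (baseline 3 s):
- μ = 6, z = 1.333: 6 × 0.9088 + 10 × 0.0912 − 3 × 0.1640 = 5.87
- μ = 4, z = 2: 4 × 0.9772 + 10 × 0.0228 − 3 × 0.0540 = 3.97
- Difference 1.90 s; loss 5%. A simulation of this case gave 1.82 s, a loss of 9%.

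**2. Power without the cap.** SD of change = 3 × √(2 × (1 − 0.5)) = 3 s, so d = 2/3. With 34 per arm, power is about 77%.

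**3. Power with the cap (simulation).** Ranges show separate runs; Monte Carlo error is a point or two.

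| Week-12 means, A v B (baseline) | At cap, A v B | Capped difference | Loss | Mean-change test | Capped data, baseline-adjusted | Censored regression with baseline |
|---|---|---|---|---|---|---|
| 6 v 4 s (3 s) | 9% v 2% | 1.90 s | 5% | 75–79% | 88% | not run |
| 9 v 7 s (6 s) | 37% v 16% | 1.49 s | 26% | 63–64% | 82–84% | 85–87% |
| 10 v 8 s (6 s) | 50% v 25% | 1.26 s | 37% | 49–52% | 78–79% | 82–85% |
| 11 v 9 s (6 s) | 63% v 37% | 1.00 s | 50% | 36–39% | 71–73% | 78–80% |
| 12 v 10 s (6 s) | 75% v 50% | 0.74 s | 63% | 21–22% | 61–63% | 72% |

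Baseline adjustment restores most of the lost power but does not undo the shrinkage: the baselines are equal in expectation, so its expected estimate on capped data is still close to the capped difference in the table. The censored regression recovers about 2.0 s. With no true difference, type I error stays near 5%.

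**4. Other assumptions.** With baseline SD 2 s, mean gains of 3.0 v 1.5 s and SD of gain 2 s, the uncapped and capped differences are:
- baseline 3 s: 1.47 and 1.39 s (power 0.86 both)
- baseline 5 s: 1.49 and 1.24 s (power 0.85 and 0.80)
- baseline 7 s: 1.49 and 0.90 s (power 0.86 and 0.64)
- baseline 8 s: 1.50 and 0.70 s (power 0.87 and 0.49)

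The direction is the same in every run; the size follows the baseline. No size was worked out for repetitions or fast contractions, where the same reasoning applies to a count.

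**The case against.** A reader might infer that the superiority hypothesis on endurance is itself tested on a truncated scale. The article does not support that. The abstract, the secondary goal and section 2.1 all assign power and endurance to the perineometer, and neither goal names PERFECT. This objection stands, and it limits the point to supporting items. It does not dispose of the point: perineometer endurance is given in pressure units, with three maximal contractions described within 4 seconds, so the PERFECT item is the only hold time in seconds that the article describes.

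A reader might also infer that the loss is certain. It is not. It requires women to reach 10, and nothing in the article says how many will. Recent pelvic floor training is an exclusion, so low baselines are plausible, and then little is lost. This stands too.

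Two further arguments stand in part. The limit of 10 is the scoring rule of the scheme as described, so change in the capped score is a legitimate quantity; a censored model instead targets an unseen hold time, adds a distributional assumption and fits integer counts poorly. That is why the censored model is proposed for endurance only. Item-level methods may also be left to an analysis plan that is not shown, but section 2.9 does name a model and no alternative to it.

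**Conclusion.** The point holds as a conditional, minor one. PERFECT endurance, repetitions and fast contractions are capped, and the only named pre/post model treats the cap as an exact value. If many women reach it, the arm difference on these items is biased toward zero and power falls. Under the SD of 3 s and true difference of 2 s, the loss runs from under 10% to about 60%; everything behind that range except the 34 per arm and the cap is assumed. The bias does not favour the high-intensity arm or inflate false positives. The perineometer endpoint and the primary outcome are untouched. Much of the recoverable power comes simply from adjusting for baseline; only the censored model corrects the estimate itself.

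**What to change.** Leave the measurement as it is and amend section 2.9 before outcome data are seen:

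- For the three PERFECT items, compare week-12 values between arms adjusted for the baseline score, in place of mean change.
- For endurance, treat 10 s as '10 or more', using a censored regression or a Cox model of time to weakening censored at 10 s, at least as a pre-specified sensitivity analysis.
- Report the share of women at the cap by arm and visit, so that a null result can be read correctly.

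This changes analysis wording only and needs no new data. The cost is a less familiar model for secondary items; the censored regression also brings a distributional assumption. If few women reach the cap, the censored and uncensored baseline-adjusted results will nearly agree and little is lost.
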